### Sample size

According to the data from the previous preliminary study, through observing the analgesic effect of opposing EA three times after TKA operation, the average VAS score was 37.0 with a standard deviation = 22.6, the average value of sham EA was 46.9, and the standard deviation was 12.5, with a significance level α = 0.05 (two-sided) and power (1 − β) = 0.8. According to the following sample size formula [44, 45], μ is the mean and σ is the standard deviation, κ = n_A_/n_B_ is the matching ratio. τ is the number of comparisons to be made. Look-up table Ζ can be obtained. The sample size was calculated as 96 cases; taking a 15% dropout rate into account, 38 subjects are required in each of the three groups.
$$ {n}_A=\left({\sigma}_A^2+{\sigma}_B^2/\upkappa \right){\left(\frac{Z_{1-\alpha /\tau }+{Z}_{1-\beta }}{\mu_A-{\mu}_B}\right)}^2 $$

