**Fig. 1 Fig1:**
[figure not shown]
The flow diagram is intended to depict the passage of participants through this RCT

The study will be sequentially conducted as follows: 114 patients in Guanghua Hospital, Shanghai University of Traditional Chinese Medicine with osteoarthritis are included (surgical contraindications are excluded); after admission, unilateral TKA will be performed as scheduled. A day before the surgery, the eligible patients will be assessed at baseline and their consent will be obtained in writing. Patients will then be randomly assigned (on a 1:1:1 ratio) to the opposing EA group, the operated side EA group, or the sham EA group. Random numbers will be generated by the SPSS 22.0 software and sealed in opaque envelopes. Only the operator in charge of acupuncture treatment is authorized to open the envelope to obtain the group code.

The three groups of subjects will receive interventions on three consecutive days after surgery, once every day, by a clinician with more than 3 years of experience in acupuncture intervention. The participants will be blinded to the intervention measures. The success of the visit would be evaluated during the last visit of each participant. Researchers who did not participate in the treatment and who did not know the allocation results will perform the outcome assessment. Unblinding before the completion of the study will only be allowed in the case of medical emergencies or severe adverse events (SAEs).

All patients will receive the same post-operative analgesic dose with a fentanyl patient-controlled analgesic (PCA) pump (continuous infusion rate 0.25 μg/(kg·h)). Additional analgesics will be provided as per each patient’s requirements ascertained by the visual analogue scale (VAS) score > 6, and the use of analgesics will be recorded in their case report form (CRF).

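### The stated sample size (96 analysable, 32 per arm, for 80% power) does not follow from the protocol's own formula and inputs, and the number of comparisons τ in that formula has no value

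*Protocol article*

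**What the plan says.** All the inputs are in the protocol article, under Sample size. For opposing EA, "the average VAS score was 37.0 with a standard deviation = 22.6"; for the control, "the average value of sham EA was 46.9, and the standard deviation was 12.5". The error rates are set "with a significance level α = 0.05 (two-sided) and power (1 − β) = 0.8". A two-mean formula follows, with allocation ratio κ and the quantile Z(1−α/τ). The text explains that "τ is the number of comparisons to be made" but gives it no value. The result is "The sample size was calculated as 96 cases; taking a 15% dropout rate into account, 38 subjects are required" per group.

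The Study design section fixes κ = 1: "Patients will then be randomly assigned (on a 1:1:1 ratio) to the opposing EA group" or one of the other two arms. It also gives the total: "114 patients in Guanghua Hospital, Shanghai University of Traditional Chinese Medicine with osteoarthritis are included". The Statistical analysis section plans a repeated-measures ANOVA for the primary outcome. The Sample size section uses no repeated-measures input and no figure for the operated-side EA arm.

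**The concern.** The protocol prints its inputs, its formula and its answer, so the answer can be checked, and it fails the check. This is not a detail left to an analysis plan: the three stated elements disagree with one another.

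The comparison sized is opposing EA against sham EA, which is central to the trial. If the printed inputs are right, the planned number does not give the stated 80% power for that comparison as the formula frames it. The chance of missing a true 9.9 mm difference would be about 42%, against the 20% that readers are told. A non-significant result could then be over-read as adequately powered evidence of no effect.

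The formula is also loosely specified. Z(1−α/τ) equals the two-sided 5% quantile only when τ = 2, and at that value it allows nothing for multiple comparisons.

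**Working it through.** **Inputs** (Sample size, except κ): means 37.0 and 46.9, difference 9.9; SDs 22.6 and 12.5; α = 0.05 two-sided; power 0.8, so Z = 0.8416; κ = 1 (Study design).

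**The plan's own figure.** 96/3 = 32 per arm. This is not printed, but the next step confirms it: 32/0.85 = 37.6, rounded up to 38, and 3 × 38 = 114. The dropout step reproduces; the 96 does not.

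**Formula as printed.** n = (22.6² + 12.5²) × ((Z + 0.8416)/9.9)². The multiplier is (510.76 + 156.25)/98.01 = 667.01/98.01 = 6.806.

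| τ | Z(1−α/τ) | n per arm | Z(1−α/(2τ)) | n per arm |
|---|---|---|---|---|
| 1 | 1.645 | 42.1 → 43 | 1.960 | 53.4 → 54 |
| 2 | 1.960 | 53.4 → 54 | 2.241 | 64.7 → 65 |
| 3 | 2.128 | 60.02 → 61 | 2.394 | 71.25 → 72 |

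**Solving backwards.** n = 32 requires Z + 0.8416 = √(32/6.806) = 2.168, so Z = 1.327. That is one-sided α of about 0.092, or two-sided 0.185, which contradicts the stated 0.05. The smallest possible τ, 1, already needs 43.

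**Other readings tried.**
- 96 as a two-arm total (48 per arm): the printed formula gives totals of 86, 108 or 122. Power at 48 per arm is 76% at two-sided 0.05, and this reading conflicts with the dropout step.
- Omnibus one-way ANOVA with pooled SD √(667.01/2) = 18.26: 51 to 67 per arm for third means of 37.0, 41.95 and 46.9. It drops to 29 only if the operated-side mean is assumed to be 32, a figure the protocol does not give.
- Settings that land near 32: SDs swapped with κ = 2 (33), SD 12.5 in both arms with α/(2×3) (34), and ANOVA with SD 12.5 in all arms and an assumed third mean of 41.95 (32). The first two contradict stated inputs. The third does so too, and also adds an unstated mean.

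**Power for a single two-group comparison, 32 per arm.** SE = √(667.01/32) = 4.566; 9.9/4.566 = 2.168. Power is Φ(2.168 − Z(1−α/(2τ))), and the difference detectable with 80% power is (Z(1−α/(2τ)) + 0.8416) × 4.566.

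| τ | Power for 9.9 mm | Detectable with 80% power |
|---|---|---|
| 1 | Φ(0.208) = 58% | 12.8 mm |
| 2 | Φ(−0.073) = 47% | 14.1 mm |
| 3 | Φ(−0.226) = 41% | 14.8 mm |

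Welch's t gives 57% at τ = 1. With all 38 per arm analysed and no split, SE = √(667.01/38) = 4.190 and power is Φ(2.363 − 1.960) = 66%.

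**The case against.** **Power under the planned analysis.** A reader might infer that the trial's real power is 58%, close to a coin toss. The documents do not support that. The 58% belongs to an unadjusted comparison at one time point, whereas the primary analysis is a repeated-measures ANOVA and VAS is scheduled on days 1, 2, 3, 5, 7 and 10. Suppose compound symmetry, a constant 9.9 mm effect and the printed SDs at every visit. Two-sided 0.05 power at 32 per arm would then be 76% (within-patient correlation 0.5) to 61% (0.9) averaging three visits, and 81% to 62% averaging six. This part stands: power under the planned analysis is unknown. It does not rescue the printed calculation, which uses no correlation and claims no such gain.

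**Which number is wrong.** A reader might also take the inputs as right and the n as wrong. The document cannot show that. With everything else as printed, an opposing-EA SD of about 15.6 would give 32 per arm at two-sided 0.05. Nothing in the text points to a misprint, but the source calculation is not visible, so it has to be checked first. This stands too.

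**The quantile.** At τ = 2 the printed term is exactly Z(0.975), so it is not wrong for every τ, and the article may have dropped a 2. That is fair. The missing value of τ and the lack of any multiplicity allowance at τ = 2 remain.

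**Intention to treat.** Analysing all 38 per arm gives 66%, still short of 80%.

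**Conclusion.** The point holds as a failure of the stated calculation. The formula and inputs give 43 to 61 per arm as printed, or 54 to 72 in the two-sided Bonferroni form, against 32 claimed. τ is undefined in value, and no τ from 1 to 3 closes the gap; a larger τ only raises n.

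The power figures of 58%, 47% and 41% are conditional. They assume the printed means and SDs, equal allocation, 32 completers per arm, the normal approximation, and one two-group comparison of opposing EA with sham EA, with no split or with α split over two or three comparisons. They describe what the protocol's sizing method delivers. They are not the trial's power under the repeated-measures analysis, for which the necessary correlation is not given.

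The paragraph should be corrected because it makes the design's central quantitative claim and its own numbers contradict it.

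**What to change.** 1. Check the two means, the two SDs and the n against the source calculation, and correct whichever was misreported.
2. If the inputs stand, keep 114 patients. Print the quantile as Z(1−α/(2τ)) and state τ with the comparisons it counts.
3. Replace the 80% claim with the pair that matches that τ at 32 per arm: 58% for 9.9 mm and 12.8 mm detectable (τ = 1); 47% and 14.1 mm (τ = 2); or 41% and 14.8 mm (τ = 3). A τ-adjusted quantile must not be paired with the unadjusted 58%.
4. Quote any gain from baseline adjustment or repeated measures only with its assumed correlation. For example, a baseline correlation of 0.5 multiplies the SE by √(1 − 0.25) = 0.866, which gives Φ(2.168/0.866 − 1.960) = about 71% at τ = 1.

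The cost is a rewritten paragraph and a less favourable stated power, with no extra patients. For comparison, keeping 80% power for 9.9 mm at τ = 1 by this method would need 54 completers per arm: 54/0.85 = 63.5, so 64 enrolled per arm and 192 in total.

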## Discussion

In recent years, with the development of fast-track (FT) surgery for joint problems, clinicians pursue the goals of painless, edema-free, stasis-free, and tubeless rehabilitation management after surgery [46]. For post-operative pain management, we should not only adopt the multi-mode analgesia model [47], but also promote the development of multi-disciplinary [48] approaches, especially by adding the high-quality analgesic methods of traditional medicine and developing the combination of traditional Chinese medicine and modern clinical medicine [49].

This clinical study of opposing needling on analgesia and rehabilitation after TKA is aimed at understanding the feasibility of such a procedure. Under the unified conditions of routine operation mode and routine intraoperative and post-operative analgesic dosage and on the premise of baseline equilibrium of the three groups, three interventions will be given according to each patient’s random number: opposing EA, operated side EA, sham EA.

Acupuncture on the affected side is a conventional non-drug therapy for rehabilitation after TKA [20, 50]. Opposing needling means applying acupuncture on the healthy leg (unoperated) of the patient, where acupoints are selected according to corresponding acupoints and meridian of the operated side. Accumulating evidence from clinical and experimental studies revealed that opposing needling exerts protective and facilitative effects on functional rehabilitation, the underlying mechanism of which remains to be further studied [51]. For patients, needling the healthy side after operation is more convenient and more acceptable. In terms of risk, needling the affected side increases the risk of infection after TKA. At the same time, the opposing needling method avoids the disadvantage of inconvenient selections of acupoints distributed at the surgical site.

In addition to the evaluation of the curative effect during hospitalization, good communication and follow-up with patients will be established. Not only will it help patients physically, but also care for patients psychologically. Through the study, we hope to provide clinicians with high-quality evidence of acupuncture for the recovery of pain and function after TKA and provide more ideas for clinicians in perioperative pain management.

## Data Availability

The datasets will be available upon reasonable request after completion of the study.

## Abbreviations

TKA: Total knee arthroplasty
EA: Electroacupuncture
KOA: Knee osteoarthritis
CPSP: Chronic postsurgical pain
SAEs: Severe adverse events
PCA: Patient-controlled analgesic
VAS: Visual analogue scale
CRF: Case report form
ASA: American Society of Anesthesiologists
ST: Stomach meridian of foot*-yangming*
SP: Foot-*taiyin* spleen meridian
GB: Gall bladder channel of foot-*Shaoyang*
HSS: Hospital for special surgery
ROM: Range of motion
COK: Circumference of the knee
HAMA: Hamilton Anxiety Scale
AEs: Adverse events
SPSS: Statistical Package for Social Science
ITT: Intention-to-treat
ANOVA: One-way analysis of variance
FT: Fast-track
